## Abstract

**Background:**

Previous research has shown that *Pinus koraiensis* leaf (PKL) extract exhibits promising anti-fatigue potential in mice, showing improved exercise endurance, decreased stress-related biochemical markers, and enhanced antioxidant activity. Based on this previous animal study, the present study aims to evaluate the efficacy of PKL extract on fatigue reduction and exercise performance in healthy adults with moderate to severe fatigue.

**Method and analysis:**

This randomized, double-blind, placebo-controlled clinical trial will enroll volunteers who meet the eligibility criteria, specifically those with a Fatigue Severity Scale (FSS) score of 27 or higher, indicating clinically significant fatigue. Eligible participants will be randomly assigned to either the PKL extract or placebo group. The intervention will consist of daily consumption of the assigned investigational product for 8 weeks, with evaluations conducted at 4-weeks intervals. Primary outcome measures include the Fatigue Severity Scale (FSS) and time to exhaustion during a treadmill exercise test. Secondary outcomes include blood fatigue markers, exercise performance parameters, rating of perceived exertion, visual analogue scale for fatigue, and grip strength.

**Discussion:**

This clinical trial aims to develop PKL extract as a functional health food ingredient for fatigue improvement. The findings will provide evidence regarding the efficacy of PKL extract for alleviating fatigue and enhancing exercise performance in humans.

## 1 Introduction

Fatigue is a common subjective symptom (1), defined in dictionaries as extreme tiredness resulting from mental or physical exertion, which distinguishes it from tiredness or sleepiness in that it occurs due to excessive effort (2). Most fatigue is alleviated by sufficient rest; however, when it persists for more than 6 months, it is referred to as chronic fatigue (3), and when accompanied by symptoms such as cognitive impairment, sore throat, tender lymph nodes, muscle pain, joint pain, headaches, non-restorative sleep, and post-exertional malaise, it is classified as chronic fatigue syndrome (4). According to a recent meta-analysis, the prevalence of general fatigue (persisting less than 6 months) in the adult population was 20.4%, while the prevalence of chronic fatigue persisting for more than 6 months was 10.1% (3). There is growing interest in effective, safe, and accessible interventions to improve these fatigue symptoms, with particular attention being given to the development of functional food from natural substances.

The physiological mechanism of fatigue is closely linked to two metabolic pathways that produce energy during exercise: anaerobic and aerobic metabolism (5). During high-intensity exercise, muscles primarily rely on anaerobic metabolism, which leads to lactate accumulation and increased lactate dehydrogenase (LDH) activity. Lactate accumulation reduces muscle pH, impairing muscle contractile function and causing fatigue (6). Additionally, creatine kinase (CK) serves as an indicator of muscle damage, increases during exercise, and is associated with fatigue (7). During prolonged exercise, aerobic metabolism predominantly contributes, with glycogen depletion, increased production of reactive oxygen species (ROS), and decreased activity of antioxidant enzymes (SOD, GSH-Px) being associated with fatigue (8). Furthermore, increased levels of the stress hormone corticosterone and decreased serotonin are related to mental fatigue. These indicators play an important role in assessing fatigue status and anti-fatigue effects.

Meanwhile, recent research has suggested the potential anti-fatigue effects of *Pinus koraiensis* leaf extract (PKL). According to a single animal study by Lee et al. (9), PKL extract improved exercise endurance in mice during weight-loaded forced swimming and rotarod tests. In terms of biochemical markers, PKL extract significantly reduced blood lactate and LDH levels related to anaerobic metabolism, as well as decreased CK levels, an indicator of muscle damage. Regarding aerobic metabolism, PKL extract significantly increased the levels of antioxidant enzymes SOD and GSH-Px, which typically decrease after exercise, demonstrating a protective effect against oxidative stress. Additionally, PKL extract improved energy metabolism by increasing glycogen levels in both liver and muscle. These results suggest that PKL extract may exert anti-fatigue effects through metabolic regulation, and antioxidant activity. Based on these promising animal findings, whether these effects also occur in humans has not yet been explored.

Therefore, this study was designed to evaluate whether the anti-fatigue effects of PKL extract observed in previous animal experiments also occur in humans. Specifically, we aim to assess the anti-fatigue and exercise performance-enhancing effects of 8-weeks PKL extract consumption compared to placebo intake in healthy adults with high fatigue levels. If the efficacy of PKL extract in humans is confirmed through this study, it could be developed as a new functional food ingredient for fatigue improvement. This clinical trial was designed as a randomized controlled trial comparing the superiority of the PKL extract group over the placebo group, with parallel comparison between the two groups, and an allocation ratio of 1:1.

## 2 Methods and analysis

### 2.1 Study setting

This clinical trial is being conducted in an academic hospital, located in Jeonju, Republic of Korea.

### 2.2 Eligibility criteria

#### 2.2.1 Inclusion criteria

This clinical trial will enroll adult men and women aged 19–60 years at the time of screening who have a Fatigue Severity Scale (FSS) score of 27 or higher. All participants must be fully informed about the clinical trial, understand its details, agree to exercise tolerance testing, and voluntarily decide to participate and comply with precautions as documented by written informed consent.

#### 2.2.2 Exclusion criteria

Participants will be excluded from the clinical trial if they have abnormal BMI (<18.5 or ≥30 kg/m^2^), clinically significant acute or chronic diseases (cardiovascular, endocrine, immune, hepatobiliary, renal, urinary, neuropsychiatric, inflammatory, hematologic-oncologic, gastrointestinal, or musculoskeletal disorders), uncontrolled hypertension or diabetes (HbA1c > 7%), tuberculosis, multiple sclerosis, hypothyroidism, uncontrolled asthma, psychiatric disorders (major depressive disorder, bipolar disorder, schizophrenia, dementia, delusional disorder), insomnia, history of renal failure, heart failure, myocardial infarction, stroke, relevant gastrointestinal diseases or surgeries, myasthenia gravis, any paralytic or atrophic myopathy, inability to perform exercise, hypersensitivity to pine nuts or pine needle components, recent use of fatigue-related products (within 1 month), exercise supplements (within 2 weeks), or antipsychotic medications (within 2 months), alcohol/drug abuse, participation in another clinical trial within 3 months, abnormal laboratory values (AST/ALT > 3 × upper limit, serum creatinine > 2.0 mg/dL), pregnancy, lactation, refusal to use adequate contraception (if applicable), or if deemed unsuitable by the principal investigator.

### 2.3 Interventions

#### 2.3.1 PKL extract and placebo capsule

Participants will receive either PKL extract or placebo capsule. The PKL is derived from the leaf of *Pinus koraiensis* Siebold & Zucc. [Pinaceae]. Each PKL capsule (680 mg) contains 480 mg of PKL extract powder. The extract has been standardized based on lambertianic acid (10, 11) as the marker compound, with a concentration of 13.53 ± 0.41 mg/g of extract powder. The placebo capsule contains no active ingredients. Both the PKL extract and placebo capsules are white opaque hard capsules containing dark greenish-brown powder. Participants will take one capsule orally once daily after dinner.

The daily dose of 480 mg of PKL extract was calculated based on preclinical studies conducted with 7-weeks old male C57BL/6 mice (unpublished data). Anti-fatigue effects were confirmed at oral doses of 50 mg/kg, 100 mg/kg, and 200 mg/kg of PKL extract. Using 100 mg/kg body weight/day as the reference animal dose, the human equivalent dose was calculated as: 100 mg/kg (animal dose) × 3 (animal Km) ÷ 37 (human Km) = 8.10 mg/kg. For a 60 kg adult, this equates to 8.10 mg/kg × 60 kg = 486 mg, which was rounded to 480 mg for the final dosage.

#### 2.3.2 Criteria for discontinuing allocated interventions

The completion status of all participants will be recorded, with documentation of reasons for discontinuation. Study participation may be terminated if: major inclusion/exclusion violations are discovered after enrollment; the participant becomes pregnant; a serious adverse event occurs or the participant requests withdrawal due to an adverse event; previously undetected systemic disease is discovered; consent is withdrawn; major protocol violations occur; the participant is lost to follow-up; difficulty with investigational product consumption arises; prohibited medications affecting study outcomes are taken; or investigators determine continued participation is inappropriate.

#### 2.3.3 Procedure for monitoring adherence

Adherence to the investigational product consumption will be monitored during the second and third visits. Participants will be instructed to bring any remaining investigational product capsules with them to these visits. The investigators will collect the remaining capsules and verify adherence by counting them.

#### 2.3.4 Permitted and prohibited concomitant interventions

Medications taken for at least 1 month prior to enrollment may be permitted if deemed not to interfere with study outcomes, and temporary medications for other conditions may be allowed; however, any medication or health functional food potentially affecting efficacy evaluation will result in participant withdrawal. During the trial period, participants are prohibited from using health functional foods related to fatigue improvement [such as plum extract (12), Rhodiola rosea extract (13), ginseng extracts (14)], exercise performance enhancers [including creatine (15), Cordyceps extract (16)], performance enhancing supplements (protein supplements, multivitamins), and medications affecting fatigue or muscle strength.

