### 2.11 Statistical methods

#### 2.11.1 Analysis set

Efficacy data will be primarily analyzed using the Per-Protocol (PP) set, with additional analyses conducted on the Intent-to-Treat (ITT) and Full Analysis (FA) sets. Safety data will be analyzed using the Safety Analysis (SA) set.

The ITT set will include all participants enrolled in this clinical trial. The SA set will comprise subjects who consumed the investigational product at least once after enrollment. The FA set will include all randomized participants with at least one efficacy evaluation after consuming the investigational product. Participants who violated inclusion/exclusion criteria or never consumed the investigational product will be excluded from the FA set. The PP set will consist of participants from the FA set who completed the trial according to the protocol without major violations. Participants who used prohibited concomitant medications or committed other serious protocol violations will be excluded from the PP set. Other serious protocol violations will be determined through a blind data review meeting.

Statistical analyses will be performed using SAS for Windows, with statistical significance set at *p* < 0.05. Missing values will be replaced using the Last Observation Carried Forward (LOCF) method. Baseline characteristics between groups will be compared using Chi-Square test or Fisher’s exact test for categorical variables and Independent *t*-test for continuous variables.

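### Stopping the product and leaving the study are written as one event, so week-8 outcomes are lost and the supporting ITT and FA analyses rest on LOCF values

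*Protocol article*

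**What the plan says.** All references are to the protocol article.

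- **Section 2.3.4** (concomitant interventions) sets an automatic rule: "any medication or health functional food potentially affecting efficacy evaluation will result in participant withdrawal". The prohibited products it lists are anti-fatigue foods, performance enhancers, protein and multivitamin supplements, and medications that affect fatigue or strength.
- **Section 2.3.2** is headed "Criteria for discontinuing allocated interventions", but its text opens "Study participation may be terminated if". Among its grounds are "difficulty with investigational product consumption arises; prohibited medications affecting study outcomes are taken". These stand in the same list as withdrawn consent and loss to follow-up.
- **Section 2.4.1** schedules FSS at baseline, week 4 and week 8, and the treadmill test at baseline and week 8 only. Both are primary outcomes.
- **Section 2.11.1** states "Efficacy data will be primarily analyzed using the Per-Protocol (PP) set", with ITT and FA as additional analyses, and "Missing values will be replaced using the Last Observation Carried Forward (LOCF) method". The PP set requires completion of the trial and excludes users of prohibited concomitant medications. The FA set requires at least one efficacy evaluation after the product has been taken.
- **Section 2.6** allows for about 30% dropout and does not divide it by cause.

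**The concern.** Two things are wrong in the text. The heading of 2.3.2 concerns the intervention, while its body concerns study participation. And for the same event, use of a product that could affect the outcomes, 2.3.4 makes withdrawal automatic while 2.3.2 leaves it to judgement. Under the discretionary reading, the investigator's decision determines whether a participant's week-8 outcome exists.

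The statistical consequence is that a change in treatment becomes missing data. The ITT and FA analyses are there to show whether the primary PP result survives once non-adherent participants and users of other products are counted. If those participants leave the study, these analyses contain only carried-forward values for them, or in the FA set sometimes nothing at all.

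Participants are enrolled because they are fatigued. Reaching for another anti-fatigue product is plausibly linked to lack of benefit, and stopping the capsules to tolerability. That is an inference; the article does not say it.

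**Working it through.** **1. The plan's own figure.** Inputs from section 2.6: mean FSS changes −9.79 and −5.20 (difference 4.59), SD 6.8, two-sided alpha 0.05, power 0.80.

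n per group = 2 × [6.8 × (1.960 + 0.842) / 4.59]² = 34.45, rounded up to 35; 35 / (1 − 0.30) = 50. Both stated figures reproduce, so the sample-size arithmetic is not at issue.

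**2. What LOCF gives a participant withdrawn before week 8.**

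| Outcome | Last value on the stated schedule | Change entered |
|---|---|---|
| Treadmill time and distance | baseline | zero |
| FSS, withdrawn before the week-4 visit | baseline | zero |
| FSS, withdrawn after the week-4 visit | week 4 | week-4 change |

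The ITT set holds all three cases. The FA set drops the second for want of any evaluation on product. It keeps the third, whose treadmill change is then zero. The PP set holds none of them, because it requires completion.

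**3. Size in the ITT set, as an illustration.** The withdrawal shares are assumptions. Everyone withdrawn is carried at baseline, and there are 50 per arm. The FSS planning figures are used because the article gives none for the treadmill. For FSS this is the unfavourable case, withdrawal before week 4.

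With a share w of an arm set to zero change and true mean change m:

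- arm mean = (1 − w) × m
- arm variance = (1 − w) × (6.8² + m²) − [(1 − w) × m]²
- SE of the difference = √[(variance active + variance placebo) / 50]
- power or rejection rate by normal approximation at two-sided 0.05

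*30% withdrawn in both arms, planned effect.* Means 0.7 × −9.79 = −6.853 and 0.7 × −5.20 = −3.640; difference 3.21. Variances 52.50 and 38.05; SE = √(90.54 / 50) = 1.346; power 0.67, against 0.92 with nobody withdrawn.

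*10% active and 30% placebo withdrawn, no true effect, both arms changing by −5.20.* Means 0.9 × −5.20 = −4.68 and 0.7 × −5.20 = −3.64; false difference 1.04 in favour of active. Variances 44.05 and 38.05; SE = √(82.10 / 50) = 1.281; ratio 0.812. Rejection = Φ(0.812 − 1.960) + Φ(−0.812 − 1.960) = 0.125 + 0.003 = 0.128.

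| Withdrawn, active / placebo | True difference | LOCF difference | Power or rejection |
|---|---|---|---|
| 0 / 0 | 4.59 | 4.59 | 0.92 |
| 10% / 10% | 4.59 | 4.13 | 0.85 |
| 30% / 30% | 4.59 | 3.21 | 0.67 |
| 30% / 10% | 4.59 | 2.17 | 0.35 |
| 10% / 30% | 4.59 | 5.17 | 0.97 |
| 25% / 35% | 0 | 0.52 | 0.07 |
| 10% / 30% | 0 | 1.04 | 0.13 |

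Equal withdrawal shrinks the difference. Unequal withdrawal can shrink it, enlarge it or create one.

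**The case against.** The strongest objections, and what remains of each:

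- **Withdrawal is mandatory only in 2.3.4.** Section 2.3.2 is permissive. A reader might infer that everyone who stops the capsules is removed from the study; the text does not support that. For capsule difficulty the loss of week-8 data is possible, not certain. This stands, and it limits the claim.
- **Informative missingness is not shown.** The prohibited list includes multivitamins and protein supplements, which people take for many reasons, and nothing in the article indicates a difference between arms. This stands: bias is a risk, not an established fact.
- **The 30% dropout has no breakdown.** It includes withdrawn consent and loss to follow-up, which no change of rule recovers. This stands, so the shares above are assumptions.
- **A condensed article may omit an early-termination visit, and the schedule figure is not shown.** That is fair, and no missing visit is alleged. But the article states the rule that ends participation, and an assessment at the time of leaving is not a week-8 outcome.
- **Retention does not buy power.** A reader might infer that observing half of the lost participants lifts analysable n from 35 to 42–43 per group and power from 0.795 to 0.86–0.87 (noncentral t, 4.59/6.8). No planned analysis makes that move. The PP set would still exclude users of prohibited medications, and LOCF already keeps the ITT set near 50 per group. The half is itself an assumption. If the 7–8 retained per group showed no effect, the difference would be about 3.7–3.8 and power about 0.71–0.72, below 0.795. Power is no part of this point.
- **The primary result hardly moves.** True. The case rests on the supporting analyses.

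**Conclusion.** The point holds in a limited form. The article states a rule that ends participation when an efficacy-affecting product is used, and its two sections disagree on whether that is automatic. Followed as written, week-8 FSS and treadmill outcomes are certainly lost for participants withdrawn before week 8 under 2.3.4, and possibly lost for others under 2.3.2. LOCF then stands in for them, with zero change on the treadmill.

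On the assumed shares, the ITT difference in FSS could fall from 4.59 to 3.21 with 30% withdrawn in each arm. With 10% against 30% withdrawn and no true effect, a false difference of 1.04 and about 13% rejection could appear. These figures rest on the assumed shares, on carrying baseline forward and on the planning SD; smaller or more equal shares give smaller errors. A later sensitivity analysis could explore assumptions about the missing outcomes but could not observe them. It is therefore too strong to say that no ITT analysis can address the problem, but right to say that collecting the outcome is better.

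**What to change.** 1. Leave the product-stopping criteria as they are, and define two separate events: stopping the investigational product, and leaving the study.
2. Ask everyone who has not withdrawn consent to attend the scheduled week-4 and week-8 assessments, with the treadmill test where the investigator judges it suitable.
3. Record each event (product stopped, other product used) and its date.
4. Use the observed values in the ITT and FA analyses in place of LOCF.
5. Reconcile the heading of 2.3.2 with its text, and *may* in 2.3.2 with *will* in 2.3.4. Which clinical rule applies is for the sponsor and investigators to decide.

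The cost is a short amendment through the IRB route in section 4.2 and a few attendances at visits already scheduled. The ITT effect may be diluted, because outcomes observed off product, or with another product, will be counted. That dilution belongs to the question an ITT analysis asks, and the PP analysis remains beside it.

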### 2.4 Outcomes

#### 2.4.1 Primary outcomes

The Fatigue Severity Scale (FSS) scores change from baseline to 8 weeks is designated as the first primary outcome (17, 18). The FSS is a self-administered questionnaire consisting of 9 items that evaluate the subjective level of fatigue-related disability on a scale of 1–7. Scores below 27 indicate “low fatigue,” scores between 27 and 44 indicate “medium fatigue,” and scores of 45 or above indicate “high fatigue.” FSS will be measured at baseline, 4 weeks, and 8 weeks.

The second primary outcome is the change in time and distance to exhaustion during a treadmill exercise test from baseline to 8 weeks. The exercise test utilizes the Modified Bruce protocol, which progressively increases both speed and incline to measure exercise capacity (19). The test begins at stage 1 (2.7 km/h, 0% grade, 3 min) and continues through predefined stages of increasing difficulty (stage 2: 2.7 km/h, 5% grade, 3 min; stage 3: 2.7 km/h, 10% grade, 3 min; stage 4: 4.0 km/h, 12% grade, 3 min; stage 5: 5.4 km/h, 14% grade, 3 min; stage 6: 6.7 km/h, 16% grade, 3 min; stage 7: 8.0 km/h, 18% grade, 3 min). The test is terminated when the participant voluntarily requests to stop. The distance to exhaustion is calculated using the total exercise duration and speed. Treadmill exercise test will be conducted at baseline, and 8 weeks.

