### 2.6 Sample size

The sample size of this clinical trial is 50 participants per group. Although no preliminary data on PKL extract’s anti-fatigue effects in humans are available, we referenced a study using fermented porcine placental (FPP) extract (26), which has received Korean MFDS approval for fatigue improvement, as PKL extract is pursuing the same regulatory pathway. In that study, the FPP group (*n* = 36) showed a mean change in FSS score of −9.79, while the placebo group (*n* = 31) demonstrated a mean change of −5.20. Based on the reference study data showing a mean difference of 4.59 points in FSS score change between treatment and placebo groups, and assuming a pooled standard deviation of 6.8, we calculated the required sample size. With a significance level of 0.05 and a power of 0.8 for a two-sided test, we estimated that a minimum of 35 participants per group would be required. Considering an anticipated dropout rate of approximately 30% during the clinical trial process, we decided to recruit a total of 100 participants, with 50 participants per group.

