### 2.9 Data collection methods

The FSS will be administered to assess the level of fatigue experienced by participants during the preceding week. Investigators will ensure that participants fully understand and can properly respond to the questionnaire. The standardized Korean version of the FSS will be used for this study (18). FSS obtained during the screening phase will be used as baseline values.

A treadmill exercise test will be conducted to measure primary outcomes including time and distance to exhaustion, along with secondary outcomes comprising AT, VO2max, RQmax, and HRmax. Additionally, RPE will be assessed at the conclusion of each stage of the treadmill exercise test, immediately before progressing to the next stage.

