## 3 Discussion

This clinical trial was designed to evaluate whether the anti-fatigue effects of PKL extract observed in previous animal experiments also occur in humans. The trial was planned in accordance with the Korean MFDS’s functional evaluation guidelines for health functional foods related to fatigue improvement (27), representing a critical step in verifying the potential of PKL extract as a functional food ingredient through human clinical trials.

The anti-fatigue effects of PKL extract are expected to work through several metabolic pathways that will be assessed using consistent biomarkers across both the previous animal experiments and this clinical trial. In mice, PKL extract showed improvements in anaerobic metabolism (reduced blood lactate and LDH activity), protection against muscle damage (reduced CK levels), and enhanced exercise endurance (increased time to exhaustion in swimming and rotarod tests) (9). This clinical trial will measure these identical objective biomarkers in humans to verify whether similar physiological responses occur, while additionally exploring subjective fatigue assessments.

If PKL extract shows significant improvements in both subjective fatigue measures and objective exercise performance parameters consistent with the animal model findings, it will provide evidence for its development as a functional health food ingredient for fatigue improvement. Furthermore, this study aims to generate the necessary data to support the regulatory approval process for PKL extract as a health functional food, bringing this natural product one step closer to benefiting public health.

There are several limitations in this protocol. First, subjective assessment tools such as the Fatigue Severity Scale and Visual Analogue Scale have inherent limitations, though this is mitigated by objective exercise performance measurements and comprehensive fatigue-related biomarkers. Second, the 8-weeks intervention period may be relatively short considering the chronic nature of fatigue (28), and the absence of follow-up limits assessment of sustained effects. Third, our strict inclusion and exclusion criteria, while creating a homogeneous study population, may limit generalizability to broader populations with fatigue, including those with different BMI ranges or chronic conditions. Fourth, as a single-center study, there may be limitations in terms of selection bias and generalizability compared to multi-center trials.

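### Three primary comparisons are each tested at 0.05 with no stated success rule, and the 0.8 power covers the FSS alone

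*Protocol article*

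**What the plan says.** Section 2.4.1 states that the 8-week change in FSS "is designated as the first primary outcome". It continues: "The second primary outcome is the change in time and distance to exhaustion during a treadmill exercise test from baseline to 8 weeks". Section 2.9 repeats that the treadmill test serves "to measure primary outcomes including time and distance to exhaustion". The body therefore has three primary comparisons: FSS, time and distance.

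The abstract is shorter: "Primary outcome measures include the Fatigue Severity Scale (FSS) and time to exhaustion during a treadmill exercise test". Distance is not named there.

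On the link between the two treadmill measures, section 2.4.1 says: "The distance to exhaustion is calculated using the total exercise duration and speed". The stage speeds and durations are preset.

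Section 2.11.1 gives one threshold, "with statistical significance set at *p* < 0.05". Section 2.11.2 compares each change score between groups by t-test or Mann-Whitney test. The article gives no split of alpha, no order of testing, and no statement of how many primaries must be significant.

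Section 2.6 uses FSS only (difference 4.59, SD 6.8, two-sided 0.05, power 0.8): "we estimated that a minimum of 35 participants per group would be required". It gives no effect, SD or power for the treadmill measures.

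The nearest text to a success criterion is a conditional sentence in the Discussion: "If PKL extract shows significant improvements in both subjective fatigue measures and objective exercise performance parameters consistent with the animal model findings", then this would count as evidence for the ingredient.

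**The concern.** With several primaries and one unadjusted threshold, the meaning of a positive trial depends on a rule that the article does not state. If one significant primary is enough, the chance of a false primary claim is well above 5%. If FSS and a treadmill measure are both needed, the error rate is safe, but the only power figure given is not the power for that outcome.

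The Discussion sentence does not settle this. It is narrative, and its terms are wide enough to cover secondary measures such as the fatigue VAS on the subjective side, or VO2max and anaerobic threshold on the objective side.

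The results are to go to the Korean food and drug ministry (section 4.5). With the rule left open, a significant treadmill result beside a null FSS could be reported as success on a primary outcome.

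**Working it through.** **1. The plan's own figure.** Inputs from section 2.6: difference 4.59, SD 6.8, two-sided alpha 0.05, power 0.8.
- d = 4.59 / 6.8 = 0.675.
- n per group = 2 × ((1.960 + 0.842) / 0.675)² = 34.45, rounded up to 35. The t-based version gives 35.44, so 36, a trivial difference.
- Inflated for 30% dropout: 35 / 0.7 = 50 per group.

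The stated 35 and 50 reproduce, for FSS at the full 0.05.

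**2. How close distance is to time.** Distance was built from the stage speeds in section 2.4.1 (2.7, 2.7, 2.7, 4.0, 5.4, 6.7 and 8.0 km/h, 3 minutes each). Treadmill times were assumed: mean 12–15 min, between-person SD 2–3 min, SD of change 1–1.5 min. The simulated correlation between change in time and change in distance is 0.97–0.99. The figures below use 0.98–0.99.

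**3. Error if any one primary counts.** All nulls true, each test two-sided at 0.05.
- Two independent tests: 1 − 0.95² = 9.75%.
- Three independent tests: 1 − 0.95³ = 14.3%. This is only a ceiling, because time and distance are far from independent.
- Correlated normal test statistics, simulated:

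| Time–distance correlation | FSS–treadmill correlation | FSS and time | FSS, time and distance |
|---|---|---|---|
| 0.98 | 0 | 9.7% | 10.6% |
| 0.98 | 0.3 | 9.5% | 10.4% |
| 0.99 | 0 | 9.8% | 10.4% |
| 0.99 | 0.3 | 9.5% | 10.1% |

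Almost all of the inflation comes from having two primaries without a rule. Distance adds about 0.6–0.9 of a percentage point.

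**4. Power if both FSS and time are needed.** The error rate needs no adjustment here. At 35 evaluable per group the mean of the FSS test statistic is 0.675 × √(35/2) = 2.824, so FSS power is Φ(2.824 − 1.960) = 0.806. The documents give no treadmill effect, so one has to be assumed:
- Treadmill d also 0.675: joint power is 0.806² = 0.65 at correlation 0, and 0.68 at 0.3.
- Treadmill d = 0.4: joint power is 0.31 at correlation 0, and 0.34 at 0.3.
- If nobody dropped out (50 evaluable per group) and treadmill d = 0.675: 0.85–0.86.

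**5. Splitting alpha instead.** With Bonferroni at 35 per group, FSS power falls to 72.0% for two tests (alpha 0.025) and 66.6% for three (alpha 0.0167). Restoring 80% takes 42 or 46 evaluable per group.

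**6. Fixed sequence.** FSS is tested first at 0.05, and time at 0.05 only if FSS is significant. Familywise error stays at 5% and FSS power stays at the value in step 1, with 35 per group unchanged. The chance of claiming both equals the joint power in step 4.

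**The case against.** The strongest counter-arguments are these.

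- *A reader might infer that the protocol must breach either 5% error or 80% power however it is read.* It need not. Step 6 shows a rule that keeps 5% overall and the stated power for FSS with no extra participants. Section 2.4.1 even labels the outcomes first and second, which could hint at an order. The objection stands against that stronger reading. It does not supply a rule, because no gatekeeping is stated.
- *A reader might infer that the 0.8 is wrong.* Section 2.6 derives it openly from an FSS difference and never offers it as the power of the whole trial. It is correct for FSS. What is missing is a statement that it goes no further.
- *Nothing says that one primary is enough, and no familywise error rate is promised.* True. The Discussion leans towards needing both, which would control the error. Its loose wording prevents it from serving as the rule.
- *The abstract is a summary.* Its verb leaves room for unlisted outcomes, so this is a loose inconsistency about distance rather than a flat contradiction.
- *Multiplicity belongs in the analysis plan, which is not shown.* The absence of a procedure would not be a point by itself. The point rests on what is printed: three primaries in the body against two in the abstract, one threshold for all, and the full 0.05 used for FSS in the sample size.

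**Conclusion.** The point holds as an unstated success rule, not as an error in the sample-size arithmetic. If any one primary counts, a false primary claim has a probability of about 9.5–9.8% with FSS and time, and about 10.1–10.6% with distance added. This is roughly double the 0.05 threshold. If FSS and time are both needed, error is controlled, but the stated power covers only the FSS half. Joint power at 35 evaluable per group would be about 0.65–0.68 under a treadmill effect as large as that assumed for FSS, and lower if it is smaller.

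The correlations and treadmill effects are assumptions, since the documents give none. The joint-power figures of 0.65–0.68 apply to the planned 35 evaluable per group and would be higher with fewer dropouts. The 14.3% for three independent tests should not be quoted as the trial's error rate.

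This should be fixed before unblinding. It does not put the recruited number in doubt.

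**What to change.** Before unblinding, and with the sample size unchanged:

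1. In 2.11, state the order: FSS change at week 8 at two-sided 0.05, then change in time to exhaustion at two-sided 0.05 only if FSS is significant.
2. Move distance to the secondary outcomes, and make the abstract, 2.4.1 and 2.9 agree.
3. In 2.6, state that the 0.8 power applies to FSS only, and that none is claimed for the treadmill outcome or for success on both.
4. Word the Discussion's claim so that it refers to these two tests.

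Requiring both FSS and time is a legitimate alternative that sits closer to the Discussion. Section 2.6 would then need a treadmill effect, an SD and a joint-power figure.

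The cost of the fixed sequence is wording, plus one real concession: a treadmill benefit without a significant FSS result could not be claimed as confirmatory.
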